### Inclusion and exclusion criteria

Inclusion criteria of the study are: 1) Age 18 years or older, 2) paid employment of at least 8 hours a week 3) not scheduled to retire in the next two years or have applied for disability pension and 4) have completed the health risk appraisal and physical testing as part of normal occupational healthcare (picture 1). All subjects have an access to Internet and are skilled in using it.

### Randomization and blinding

Randomization will take place at an individual level. A biostatistician will prepare the randomization scheme by using a computer-generated randomization table. Block randomisation with blocks of ten will be applied. Based on the randomisation scheme, two research assistants will prepare sealed envelopes before the start of the study containing either a referral to the intervention group or control group. After signing the informed consent form, each employee will open a sealed envelope in the given order. The researchers will not be able to identify the group assignments before the randomisation. Due to the nature of the interventions, the participants and researchers will not be blinded for the group assignment after randomization. Employees will not be allowed to change groups after randomization. Sickness absence data will be extracted from the company records in an electronic format and self-reported data will be entered into the computer by a research assistant, which will ensure blinded analysis of the data by the researchers.

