### Sample size

The standard deviation for the IPAQ score in our population was estimated to be 1500 MET min-per-week. A difference of 400 MET min-per-week between treatment arms will be detectable with 85% power in two-tailed tests with the alpha of 0.05 for a sample of 253 employees in each group; the standardized effect size will be 0.25.

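### A single fixed block of ten, with envelopes opened in sequence and open allocation, leaves concealment weakened and not assured, although the protocol states it without qualification

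*Protocol article*

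**What the plan says.** The procedure is in the protocol article under Randomization and blinding. The unit is the individual ("Randomization will take place at an individual level"), and no stratification factor or site is named. The list has a sound origin: "A biostatistician will prepare the randomization scheme by using a computer-generated randomization table". One block size is given: "Block randomisation with blocks of ten will be applied". From this scheme "two research assistants will prepare sealed envelopes before the start of the study". After signing consent, "each employee will open a sealed envelope in the given order".

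Two further statements matter. On concealment: "The researchers will not be able to identify the group assignments before the randomisation". On blinding after allocation: "the participants and researchers will not be blinded for the group assignment after randomization".

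The section does not say that block sizes vary, that the block size is kept from recruiting staff, or that the assistants who fill the envelopes take no part in recruitment.

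**The concern.** With a fixed block size, each block must end in balance, so past assignments carry information about the next one. Sealing the envelopes does not remove this, because the information comes from envelopes already opened. Past assignments are visible to the researchers by the protocol's own statement, and only intervention employees receive an activity monitor (Intervention group section). The two assistants have a more direct route: they prepare the envelopes from the scheme and so have seen the list.

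The stake is selection bias. Employees are invited and consented one by one after physical testing, and may ask questions before deciding (opening of Methods/Design). Someone who foresaw the next arm could, knowingly or not, encourage or delay consent. Physical activity, the first of the primary outcomes listed, is self-reported by questionnaire, and the Discussion concedes that no other measure of change covers the whole study population. If more motivated employees entered one arm, that comparison would be distorted, and an intention-to-treat analysis would not correct it.

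**Working it through.** **Inputs.** Block size 10 (Randomization and blinding). Ratio 1:1 within blocks, inferred from equal planned arms ("for a sample of 253 employees in each group", Sample size). Total 2 × 253 = 506. Assumed, because the document does not state it: one allocation list, and an observer who knows the block size and every earlier assignment.

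**The plan's own figure.** n per group = 2 × (1.960 + 1.036)² × (1500/400)² = 2 × 8.98 × 14.06 = 252.5, rounded up to 253. The stated sample size is reproduced. It serves here only to scale the count; sample size and power are unaffected by this point.

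**Assignments known with certainty.** A 1:1 block of ten has C(10,5) = 252 equally likely orders. An assignment is certain when all remaining places belong to one arm:
- 10th: 252/252
- 9th: 2 × C(8,3) = 112, so 112/252
- 8th: 2 × C(7,2) = 42, so 42/252
- 7th: 2 × C(6,1) = 12, so 12/252
- 6th: 2/252
- 1st to 5th: none

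The sum is 420/252 = 1.67 per block, or 16.7%. This agrees with 2m/(m+1) for m = 5. Scaled to the trial: 506 × 0.1667 = 84. Counting only the 50 complete blocks gives 50 × 1.67 = 83.

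**Average guessing accuracy.** Always guessing the arm with fewer assignments so far gives m + 2^(2m−1)/C(2m,m) − 1/2 = 5 + 512/252 − 0.5 = 6.53 correct per ten, or 65.3%, against 50% by chance.

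**Comparison of schemes.** Fixed blocks by full enumeration. Random sizes by 300 simulated lists of 506, with an observer who knows the possible sizes but not the current one.

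| Scheme | Known with certainty | Guessable with at least 75% probability | Best guess correct |
|---|---|---|---|
| Fixed 4 | 33.3% | 33.3% | 70.8% |
| Fixed 10 (the plan) | 16.7% | 23.9% | 65.3% |
| Random 6/8/10 | about 1.5% | about 25.9% | about 66.4% |
| Random 8/10/12 | about 1.2% | about 20.7% | about 65.2% |

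Hidden random sizes nearly remove certain knowledge: with 8/10/12, 506 × 0.012 is about 6 assignments instead of about 84. They do not lower average guessing accuracy.

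**The case against.** The strongest reply is that the described concealment is real. A biostatistician generates the list, the envelopes are sealed before the start, and the employee opens one only after signing. Ten is a fairly large block, less predictable than a fixed four. Even a perfect tracker could not deduce about five assignments in six.

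The participant flow also leaves little scope for steering. All employees are first approached by one mass e-mail, they book their own test times through a web link (both under Eligible population), and the trial invitation follows from completing the test. The document nowhere says that recruiting staff know the block size, see every earlier assignment or draw on one list. A full protocol may well withhold the block size from them.

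Most of this stands. A reader might infer that staff will work out upcoming assignments, that concealment fails, or that selection bias passes straight into the main comparison. The document supports none of these: the tracking conditions are assumptions, and no bias in MET-minutes can be calculated from what is given. A reader might also take the 65% guessing rate as a harm that varying the block size would remove; the table shows that it would not.

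The reply does not rescue the unqualified assurance. Opening after consent stops an assignment from being changed, but not from being foreseen before consent is sought. The assistants' sight of the scheme does not depend on counting blocks at all.

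**Conclusion.** The point holds in a limited form: concealment is weakened and not assured, and the article claims more than its procedure guarantees. The size is about one assignment in six known in advance (about 84 of 506), including the last of every block. This rests on a single 1:1 list and on an observer who knows the block size and tracks the sequence. Parallel testing streams drawing on the same sequence, or a block size kept from recruiting staff, would lower it. What room there is for bias lies mainly in influence on whether or when a tested employee consents. The change is worth making because it costs almost nothing, not because bias has been shown.

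**What to change.** Specify permuted blocks of randomly varying size, for example 8, 10 and 12, with the sizes known only to the biostatistician and withheld from staff who test, invite or consent employees. State also that the two research assistants who prepare the envelopes take no part in inviting or consenting. That separation is needed whatever the block sizes are.

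The cost is a regenerated list before the start and two sentences of text, with no extra participants. The arms may differ by a few participants if recruitment stops within a block: at most 6 with a largest block of 12, against 5 with blocks of ten. The gain is the fall in certain knowledge from 16.7% to about 1%; average guessing accuracy stays at about 65%.

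If the list can no longer be changed, qualify the concealment statement and say who knew the block size and who had seen the scheme.

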### Physical testing

A background questionnaire concerning medical history and medication is filled in before physical testing. Employees can be excluded before or during the physical testing for multiple medical reasons: pregnancy, diagnosis or treatment of cancer, any disorder that makes physical activity impossible. Complete list of exclusion criteria is listed in Appendix 1. The test is started by measuring one's height, weight, waist circumference, body fat percentage and blood pressure. All measures are taken with previously validated measures and are described in more detail later. Aerobic fitness is measured by means of the indirect bicycle ergometer test (Aino Fitware). The test gives a prediction of the maximal oxygen uptake (VO2 max) during maximal exertion. The employee is asked not to eat, drink or smoke for 2 hours before this test. During the bicycle ergometer test the subject must report his/her subjective rate of exertion at the end of each stage using a scale of 6 to 20 [25]. The test is terminated when the pedalling rate drops under 60 rounds per minute. The estimated VO2 max is calculated with software analysis program (Aino Fitware). The AA Fitware test uses common validated procedures and measures from previous studies [26].

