**SECONDARY OUTCOMES**					
Body weight	M	v	v	v	
Body height	M	v			
Waist circumference	M	v	v	v	
Body fat percentage	M	v	v	v	
Blood pressure	M	v	v	v	
Aerobic fitness; VO2 Max	M	v	v	v	
Programme costs	R				

Q = Questionnaire, M = Measurement, R = Registry

Assessment of the secondary outcomes is done either by questionnaire, measurements during the physical test, or by collecting data from occupational healthcare provider and employer's absenteeism/payment records.

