#### Waist circumference

Waist circumference (in cm) is measured twice with a measuring tape (Reiju Oy) with a range of 0-150 cm. Waist circumference is measured to the nearest 0,5 cm, at the midpoint between lower border of the ribs and the upper border of the pelvis. A means value of the two measurements is computed.

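### No masking is provided for whoever takes the measured 12-month secondary outcomes, and the reason given for open allocation does not require those testers to know the arm; tape-read waist circumference is the most exposed.

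*Protocol article*

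**What the plan says.** The section Randomization and blinding of the protocol article takes a position: "Due to the nature of the interventions, the participants and researchers will not be blinded for the group assignment after randomization". The same section then offers one safeguard. Sickness absence comes electronically from company records, and "self-reported data will be entered into the computer by a research assistant, which will ensure blinded analysis of the data by the researchers". Nothing is said there about outcomes measured on the person.

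Table 2 marks those outcomes with M for measurement. Body weight, waist circumference, body fat percentage, blood pressure and aerobic fitness are all scheduled at baseline, 6 and 12 months; for example "Waist circumference M v v v" and "Aerobic fitness; VO2 Max M v v v". The note under the table says: "Assessment of the secondary outcomes is done either by questionnaire, measurements during the physical test".

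The methods differ in how far they depend on the person measuring:

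- Waist is a manual reading: "Waist circumference (in cm) is measured twice with a measuring tape (Reiju Oy) with a range of 0-150 cm", and "Waist circumference is measured to the nearest 0,5 cm" at a midpoint the tester has to locate.
- For fitness, the Physical testing section says: "During the bicycle ergometer test the subject must report his/her subjective rate of exertion at the end of each stage". The test ends when the pedalling rate falls below 60 per minute, and software then estimates VO2max.
- Weight is taken on a digital scale, body fat with an analyser and blood pressure with a fully automated monitor.

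**The concern.** The nature of the intervention is a sound reason for leaving participants and coaches unblinded. It is no reason for a tester to know the arm. The masking on offer acts at data entry and analysis, and it cannot undo a bias that enters when the tape is read.

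The design also gives testers ways to learn the arm. Participants in the intervention group receive a monitor that can be attached to a belt. The Intervention group section describes a 6-month physical test, while the Control group section mentions none. Table 2 ticks 6 months without naming an arm. If the Intervention group section governs, a 6-month result on file identifies the arm at 12 months.

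The Discussion concedes that change in activity across the whole population can be followed only by a questionnaire that may be rather insensitive. Readers will therefore look to the measured outcomes for physiological support that is not self-reported. The Statistical analyses section promises an effect estimate with a confidence interval for each of them.

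**Working it through.** **1. What the blinding section covers.**

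| Type of data | Masking stated |
|---|---|
| Sickness absence (register) | At analysis |
| Self-reported data (questionnaire) | At analysis |
| Measured outcomes (M in Table 2) | None stated, at measurement or at analysis |
| Identity of 12-month testers and their knowledge of the arm | Not stated |

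**2. Which measured outcomes a tester can move.** Waist is the clear case: a hand-held tape, a landmark found by the tester and a 0.5 cm reading step. Averaging two readings reduces random error, but not a shift common to both. VO2max is less direct: software computes it, but from a test that depends on effort. Weight, body fat and blood pressure are read by a device.

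**3. The plan's own sample size.** The Sample size section gives SD 1500, difference 400, 85% power, two-sided alpha 0.05 and 253 per group.

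n = 2 × [(1.960 + 1.036) × 1500/400]² = 252.5, so 253 per group. The figure reproduces, with power 85.1%. It is the target for the activity score and is used below only as a convenient group size. The number tested at 12 months may be lower.

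**4. Illustration of the effect of a shift.** The document gives no SD for waist or VO2max, so every SD, correlation and shift here is an assumption.

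- SE = SD × √(1 − r²) × √(2/253), where r is the correlation with baseline (r = 0 means no adjustment) and √(2/253) = 0.0889.
- False-positive rate with no true effect and a systematic between-arm shift b: P(|Z + b/SE| > 1.96).

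| Outcome | Assumed SD | Assumed r | SE | b = 0.5 | b = 1.0 |
|---|---|---|---|---|---|
| Waist (cm) | 12 | 0 | 1.067 | 7.6% | 15.5% |
| Waist (cm) | 12 | 0.8 | 0.640 | 12.2% | 34.6% |
| Waist (cm) | 12 | 0.9 | 0.465 | 18.9% | 57.5% |
| Waist (cm) | 8 (residual) | – | 0.711 | 10.8% | 29.0% |
| Waist (cm) | 4 (residual) | – | 0.356 | 29.0% | 80.3% |
| VO2max (ml/kg/min) | 7 | 0 | 0.622 | 12.7% | – |
| VO2max (ml/kg/min) | 7 | 0.8 | 0.373 | 26.8% | – |

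Worked line: waist SD 12, r = 0.9 gives 12 × √(1 − 0.81) × 0.0889 = 0.465; 0.5/0.465 = 1.075; P(|Z + 1.075| > 1.96) = 18.9%. The residual rows put the SD straight into the formula without a correlation term.

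A 0.5 cm shift therefore gives about 8% to 29% in place of 5%. It equals one reading step, as an average difference between the arms.

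**The case against.** A reader might infer that nobody who measures the 12-month outcomes is masked. The document does not support that. It names participants and researchers, not testers, and no section says whether testers count as researchers. One can also argue that tester identity is operational detail a journal article leaves to its full protocol. That would be decisive if the article were silent on blinding. It is not: it states who is open, why, and which data are protected, and the measured outcomes fall outside that protection.

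A reader might also infer that the measured outcomes as a group are unsafe, or that testers could manufacture a VO2max effect. Neither is supported. Three of the measurements are device-read. VO2max is software-estimated, encouragement by the tester is nowhere described, and an unblinded participant's own effort can bias the result even with a masked tester. Nor does the article say that the monitor is worn at the 12-month test, or that testers and coaches are the same people.

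The error rates are open to a fair objection too: any trial shows inflation once a systematic shift is assumed, and nothing in the document shows that a shift of 0.5 cm would occur. This stands, and the figures show sensitivity only.

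Finally, all the affected outcomes are secondary. The primary outcomes come from questionnaires or registers, and the latter also supply evidence that is not self-reported. This limits the weight of the point but does not remove it.

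**Conclusion.** The point holds in a limited form. The blinding plan gives the measured 12-month secondary outcomes no protection at measurement, and its stated reason does not require testers to know the arm. Whether they would know it is unstated. The main exposure is waist circumference, with ergometer VO2max second. The primary outcomes are untouched.

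The 8% to 29% range for a 0.5 cm waist shift shows that a small systematic bias could matter at this sample size. It does not estimate how likely such a bias is. The change is worth making because it is cheap and because detection bias of this kind cannot be repaired in the analysis.

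**What to change.** Add to Randomization and blinding:

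- The 12-month measurements are taken by existing test staff who are kept unaware of allocation and are not the participant's coach.
- They work from a test list that does not show the arm, and they do not see 6-month results.
- Participants leave the monitor off for the test and are asked not to mention their group.
- Any unmasking is logged and reported by arm.

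Where VO2max is reported, state that participants knew their arm and that their own effort may have affected the result.

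The cost is instructions and some scheduling. Because the article does not say who tests, the sponsor should confirm that staff other than the coaches are available. Masking will sometimes fail; the log shows how often. No new outcome or procedure is needed.

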#### Intervention group

After the physical testing employees assigned to the intervention group will receive their test results and information on physical activity. They will also receive a physical activity monitor (PAM, model AM 200, PAM BV, the Netherlands), which is an uni-axial accelerometer in the vertical direction that can be easily attached to a belt. The validity of the PAM accelerometer has been tested in a laboratory setting and has shown results similar to the MTI actigraph for estimating energy expenditure in walking and stair walking [27]. The PAM produces a single index score that accumulates during the day and is a proxy measure of total daily PA. The PAM shows the PAM score continuously on its display.

The participants have to install the PAM software on their computer in order to use the PAM reader. Via a USB cable, which must be connected to a computer with an internet connection, the user can upload his or her personal PAM scores through PAM software to the Aino Active (AA) website http://www.ainoactive.fi at any time throughout the day. When reading the PAM, the participant is automatically directed to the AA website. During the first visit, the user will register on the AA website by filling out a form with personal data (ie, username and password). Upon entry to the website, the user formulates a PAM goal score for the 12 month intervention period. Based on the first two weeks the employee and AA's coach can together decide to change the PAM goal. The PAM goal score can be changed by the user and AA's coach throughout the intervention. On every subsequent log-in, the AA's website presents all the uploaded PAM scores and coupled PAM goals in orderly graphs per week or month.

On the Aino Active website, users can interactively plan and evaluate their own activity advice based on their actual PAM scores and their PA goals and preferences. When an employee does not log on to the site every two weeks to download activity data she/he receives a phone call from the coach. The subjects in the intervention group will also participate in a physical test at 6 months of the intervention. Their occupational health care is continued as usual.

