### Statistical analyses

The effect of the intervention will be estimated on an individual level based on the intention-to-treat principle. For each primary and secondary outcome, a summary of results for each group, and the estimated effect size and its precision with confidence intervals will be presented. We will also assess potential effect modifying and mediating factors. The potential modifiers and mediators have been predefined and will all be measured at baseline. The potential effect modifiers are personal characteristics (age and gender), the result of the health risk appraisal (high/intermediate/low risk), baseline self-rated level of physical activity, baseline level of the ergometer test; job characteristics (specialist/manager), sick-leave related characteristics (sick leave days in the past year), and self-rated disability thoughts. The potential effect mediating factors are attendance to the PA intervention as intended, healthcare utilisation, and sick-leave related characteristics (sick leave days during the follow-up year).

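### Data entry by a research assistant and electronic extraction cannot ensure blinded analysis by researchers whom the same section calls unblinded

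*Protocol article*

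**What the plan says.** The section Randomization and blinding of the Protocol article makes three separate statements.

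- Concealment before allocation: "The researchers will not be able to identify the group assignments before the randomisation". This rests on sealed envelopes prepared from the randomisation scheme.
- Conduct after allocation: "the participants and researchers will not be blinded for the group assignment after randomization". The reason given is the nature of the interventions.
- Analysis: absence data come from company records in electronic form, and "self-reported data will be entered into the computer by a research assistant, which will ensure blinded analysis of the data by the researchers".

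Other sections plan data that bear on the arm. Statistical analyses states: "The potential effect mediating factors are attendance to the PA intervention as intended". Table 2 lists programme costs as a registry-based secondary outcome, and Cost-effectiveness analysis counts the cost of delivering the programme. The section Intervention group says of that arm "They will also receive a physical activity monitor (PAM, model AM 200, PAM BV, the Netherlands", and adds: "The subjects in the intervention group will also participate in a physical test at 6 months of the intervention". Table 2 ticks weight, waist, body fat, blood pressure and aerobic fitness at 6 months without naming an arm.

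**The concern.** The analysis sentence promises a property and names the means of achieving it. The means concern who types in the questionnaires and how the absence records are pulled. Blinded analysis depends on something else, namely whether the analyst can tell which participants belong to which arm.

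The promise matters because physical activity is reported by participants who know their group. Blinded analysis is then one of the few protections that the article claims, and readers will give credit for it. An analyst who knows the arms can be influenced in analytic choices and in emphasis. The article lists several primary outcome domains, and Table 2 has several follow-up times, although the Background names 12 months for the main purpose.

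**Working it through.** No figure in the plan enters this point, so the check sets the statements side by side.

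**Step 1. Who is unblinded, and who analyses?** Both sentences use the same term, the researchers. After randomisation they know the assignments, and they are also the people said to analyse blind. No separate analyst is mentioned. A biostatistician appears, but only to prepare the randomisation scheme.

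**Step 2. What can the two named steps achieve?**

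| Step | What it can do | Does it hide the arm from the analyst? |
|---|---|---|
| Electronic extraction of absence data | Limits influence on, and error in, data capture | No |
| Questionnaire entry by a research assistant | Keeps the researchers away from transcription | No |

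A file made by both steps can still carry the arm in plain form.

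**Step 3. What would be needed?** The arm would have to be coded, the key withheld until the main comparison is done, and variables that reveal the arm kept out of the file. The article describes none of these. Concealment before allocation is a different safeguard and does not supply them.

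**Step 4. Would a coded file stay masked?** That depends on what is merged into it.

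| Variable | Where planned | Reveals the arm? |
|---|---|---|
| Attendance at the intervention | Statistical analyses (mediator) | Yes, it has meaning in one arm only |
| Programme costs | Table 2; Cost-effectiveness analysis | Yes, if held per participant, since only one arm receives the programme |
| 6-month physical test | Intervention group; Table 2 | Only if the test is done in one arm, which the article does not settle |
| Activity questionnaire, productivity, absence | Table 2 | No, these are held in both arms |

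The last row shows that a masked comparison of the main outcomes is feasible. The first two rows show that it would be lost if the mediator or the cost data were merged first.

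**The case against.** The best defence is that an open-label trial can still have a masked analysis. The statement that researchers are unblinded concerns trial conduct, while blinded analysis concerns the file that the analyst receives. A journal article may also leave arm codes and data release to a full protocol or analysis plan that is not shown here. Part of this stands: the two sentences can be reconciled if a coding step exists, and silence about that step would not be a fault in itself. But the article is not silent. It gives a mechanism and says that the mechanism ensures the result, which it does not.

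Several stronger readings are tempting, and the document does not support them.

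- *The research database holds monitor scores and log-ins.* The consent paragraph of Methods/Design names health risk appraisal, physical testing, healthcare utilisation and absence records as the registers that feed the database. Monitor scores are uploaded to the programme's website, and no listed outcome uses them.
- *The 6-month test marks the intervention arm.* It is described for that arm and not for controls, but Table 2 does not restrict it to one arm.
- *The person entering data knows the allocation list.* The article says that "two research assistants will prepare sealed envelopes before the start of the study containing either a referral to the intervention group or control group", but does not say that one of them enters the data. What that person knows would not settle what the analyst knows in any case.
- *The choice between raw and truncated MET minutes is left open to an unblinded analyst.* The section Physical activity defines the total score first and introduces the truncated score as an addition, which suggests that it is supplementary.

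**Conclusion.** The point holds as an incorrect assertion: the article claims blinded analysis on the strength of two steps that do not provide it, in a section that also calls the researchers unblinded. Attendance and programme costs are planned variables that would unmask a coded file if merged before the main comparison. This assumes that both are held per participant. Nothing in the article says that they will be in the file used for that comparison, so this is a risk to exclude and not a demonstrated breach.

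The size of any analyst bias cannot be computed from the document. A reader might infer that the arm can be recovered for the whole planned intervention group of 253. That figure is only the planned group size, and the inference rests on database contents and a one-arm 6-month test that the article does not establish. Nor would a masked analysis remove reporting bias from participants who know their group. The trial remains valid, and the fault is that a stated safeguard is not delivered by the procedure described.

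**What to change.** Replace the sentence with a procedure that masks the analyst:

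1. The biostatistician releases an outcome file with the arm coded A/B and without attendance, programme costs or any other variable that exists only for the intervention group.
2. The 6-month measurements stay in that file if they are taken in both arms, as Table 2 suggests. They are withheld until unmasking only if they are taken in one arm.
3. The primary between-arm comparison is fixed and run on that file before the code is broken.
4. The mediation and cost analyses are described as unblinded.

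If this is not done, delete the claim of blinded analysis. The change costs some protocol wording and a data release in two stages, with a short delay before process and cost data can be analysed.
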